### Plans for collection, laboratory evaluation**,** and storage of biological specimens for genetic or molecular analysis in this trial/future use {33}

See above 26b, there will be no biological specimens collected.

## Statistical methods

### Statistical methods for primary and secondary outcomes {20a}

Data will be stored in SAS data files and statistical analyses will be conducted using SAS. We will use an intent-to-treat analysis for our primary and secondary analyses. At baseline, post-intervention, and 8-week follow-up time points, standard descriptive statistics will be calculated for degree of impairment (FMUE) and degree of function (CAHAI-9). We will also compute standard descriptive statistics for less severely impaired participants (FMUE 30-38) and the more severely impaired participants (FMUE 23-29) as determined at baseline. We will assess the relationship between both FMUE and CAHAI-9 at baseline and time since stroke, age, and gender. In addition, we will examine the correlation between changes in FMUE and CAHAI-9 from baseline to follow-up time points (end of intervention and 8 weeks post-treatment cessation) and time since stroke, age, and gender. We will report pairwise correlations and standard errors for these descriptive analyses.

Confirmatory analyses will largely use normal theory methods based on analysis of covariance. We will use residual diagnostics to evaluate model fit and take appropriate data transformations as necessary.

#### Hypothesis 1a and 1b analysis

For each dependent measure (FMUE and CAHAI-9), primary confirmatory analyses will compare the experimental group (BMP+TST) versus the control group (CP+TST). We will use normal linear models with effects for treatment assignment and the outcome measure at baseline, equivalent to an analysis of covariance. We will report point estimates and standard errors of these differences and conduct two-sided null hypothesis tests at the 5% level (*α* = 0.05).

#### Hypothesis 2a and 2b analysis

Descriptive statistics for Hypotheses 2a and 2b will follow a similar approach as those for 1a and 1b, but we will focus on TCI as our outcome of interest. Confirmatory analyses will analyze differences in TCI between treatment arms at 8 weeks post-treatment cessation. We will report estimated differences between treatment arms along with standard errors. We will also conduct two-sided hypothesis tests at the 5% level. For 2b, we will perform a correlation to determine the relationship between changes in ipsilesional TCI and FMUE from pre to follow-up.

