### Objectives {7}

The purpose of this study is to test the hypothesis that bilateral symmetrical arm movements prime cortical regions and enhance neuroplasticity as measured by behavioral and cortical measures. Specifically, this trial will address two main objectives and test their associated hypotheses. The primary objective is to determine the magnitude of change in upper limb function and impairment in chronic stroke survivors who have undergone 30 h of BMP + TST. Primary hypothesis 1.1 is that the combination of BMP + TST will produce a between-group difference in improvement on the FMUE of at least 6.0 points more than control priming (CP) + TST at the follow-up timepoint (8 weeks post-treatment cessation). Secondary hypothesis 1.2 is that the combination of BMP + TST will increase scores on the Chedoke Arm & Hand Activity Index (CAHAI-9) by 3 points more than CP + TST, 8 weeks after the post-test (follow-up).

The secondary objective is to determine the effects of bilateral priming on cortical mechanisms measured by TMS. Hypothesis 2.1 is that BMP + TST will increase TCI from ipsilesional to contralesional hemisphere at post-treatment (following 30 h of treatment) and at 8 weeks after treatment cessation (follow-up), but there will be no change in the CP + TST group. Hypothesis 2.2 is that an increase in ipsilesional TCI will be positively associated with changes in the FMUE. We will perform a correlation analysis to test this relationship.

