### Sample size {14}

We are enrolling 38 subjects per group (*N* = 76). Allowing for the attrition of 12 participants (15% based on our pilot study [13]), we project at least 32 subjects per group will have both the baseline and follow-up data required to compute our change outcomes at 8 weeks post-treatment cessation. For the hypotheses tested for objectives 1 and 2, we will evaluate between-group (BMP+TST vs. CP+TST) differences using analyses of covariance (ANCOVA) that adjust for the outcome measure at baseline; tests will be two-sided at the 5% level (*α* = 0.05). The power of these tests depends on the number of participants in each group, the separation of the means of each group, the significance level, the population standard deviation (SD) of the outcome measures, and the correlation between measures at baseline and follow-up. We consider what sample size per group (*n*) will provide 90% or greater power.

We discuss each of the two objectives in turn. Table 2 presents the primary outcome measure (FMUE), secondary outcome measure (CAHAI-9), and the additional outcome measure (TCI in objective 2). For each measure, the table shows the difference in the group means that can be detected with 90% power assuming *N*=32 per group, along with the hypothesized SD of the outcome. Power computations assume a modest correlation between baseline and follow-up for measures of *R*^2^ = 0.2. To derive our estimates of the SD of outcome measures at follow-up (8 weeks post-treatment cessation), we used the results of a published pilot study at 6 weeks post-treatment cessation [13].

**Table 2 Tab2:** Sample size analysis: primary and secondary measures

	Mean difference	SD

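### The correlation planned for hypothesis 2.2 names no adjustment for treatment arm, so across all participants it would partly restate hypotheses 1.1 and 2.1

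*Protocol article*

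**What the plan says.** Objectives {7} of the protocol article places the hypothesis under the secondary objective, which concerns cortical mechanisms: "Hypothesis 2.2 is that an increase in ipsilesional TCI will be positively associated with changes in the FMUE". It adds: "We will perform a correlation analysis to test this relationship". The section Hypothesis 2a and 2b analysis, where 2b is the same hypothesis, gives the variables and the time window: "For 2b, we will perform a correlation to determine the relationship between changes in ipsilesional TCI and FMUE from pre to follow-up". Neither place mentions treatment arm, a partial correlation or within-arm correlations.

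Objectives {7} also predicts how the arms will differ on each variable. For FMUE, hypothesis 1.1 expects a "between-group difference in improvement on the FMUE of at least 6.0 points more than control priming (CP) + TST". For TCI, hypothesis 2.1 expects a rise with BMP plus task-specific training, "but there will be no change in the CP + TST group".

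Elsewhere the article states an arm term where one is wanted: in the ANCOVA for FMUE and CAHAI-9 (Hypothesis 1a and 1b analysis) and in the exploratory regressions (Methods for additional analyses {20b}). Those regressions take FMUE, CAHAI-9 and TCI as separate outcomes. None relates TCI change to FMUE change.

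**The concern.** If BMP raises both FMUE and TCI, the two arms separate in the same direction on both axes of the scatterplot. A correlation across all participants picks up that separation as well as any link between the two changes among people given the same treatment. The between-arm part adds nothing new, because hypotheses 1.1 and 2.1 already test it. It also cannot distinguish a gain in arm impairment that runs through transcallosal inhibition from two parallel effects of the same treatment. Only the within-arm association bears further on the mechanism. The problem is largest when the trial succeeds on both outcomes, which is when the correlation is most likely to be cited.

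**Working it through.** **Inputs.** Sample size {14} projects 32 evaluable participants per arm ("we project at least 32 subjects per group will have both the baseline and follow-up data") and states that "tests will be two-sided at the 5% level". Table 2 gives a difference and SD of 5.98 and 8.11 for FMUE and 2.74 and 3.71 for TCI, with the SD labelled as that of the change score. The pilot change SDs for FMUE, from Background and rationale {6a}, are 6.1 and 4.1. The article gives no figure for the 2b correlation itself.

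**The plan's own figures.** With R² = 0.2 the ANCOVA residual SD for FMUE is 8.11 × √0.8 = 7.25, and the standard error of the difference is 7.25 × √(2/32) = 1.81. Solving the noncentral t for 90% power gives detectable differences of 5.97 (FMUE), 5.35 (CAHAI-9) and 2.73 (TCI), against 5.98, 5.34 and 2.74 stated. Table 2 reproduces. Its entries are solutions of a power equation: "the table shows the difference in the group means that can be detected with 90% power assuming *N*=32 per group". The TCI value of 2.74 is therefore a detectable difference and not a predicted effect.

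**Formula.** Let dF and dT be the between-arm shifts in FMUE change and TCI change, in within-arm SD units, with 1:1 allocation and zero within-arm correlation. The arm indicator has variance 1/4, so the expected correlation over all participants is

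r = (dF × dT / 4) / √[(1 + dF²/4)(1 + dT²/4)].

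Its sign is that of dF × dT, and it is zero if either shift is zero.

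**Table 2 differences.** dF = 5.98/8.11 = 0.737 and dT = 2.74/3.71 = 0.739. The numerator is 0.136 and the denominator 1.136, so r = 0.12. A Fisher-z check gives atanh(0.12) × √(64 − 3) = 0.94, and P(Z > 1.96 − 0.94) is about 15%. Simulation (40,000 trials) gives 15.7%, almost all in the positive direction.

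**Pilot-based FMUE SD.** Pooling 6.1 and 4.1, assuming equal arm sizes, gives √[(37.21 + 16.81)/2] = 5.2. With the hypothesised 6.0 points, dF = 6.0/5.2 = 1.154. With dT = 0.739, r = 0.213/1.231 = 0.17. Simulated rejection is about 28–29%.

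**Range.** All rows assume zero within-arm correlation and 32 per arm.

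| Assumed shifts (TCI, FMUE) | Expected r | Rejection at nominal 5% |
|---|---|---|
| 0.739, 0 (one outcome moves) | 0.00 | 5% |
| 0.5, 0.5 | 0.06 | 8% |
| 0.739, 0.737 (Table 2) | 0.12 | 16% |
| 0.739, 1.154 (FMUE SD 5.2) | 0.17 | 28–29% |
| 1.0, 1.0 | 0.20 | 36% |

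At the Table 2 shifts, 20 to 38 evaluable participants per arm give 11% to 18%.

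**With arm partialled out.** The mean correlation is 0.00 and the test rejects about 5% of the time in every scenario simulated.

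**The case against.** The strongest reply is that the article says only that a correlation will be done. It does not say pooled, unadjusted or Pearson, and an analysis plan that is not shown could condition on arm. This stands in part. A reader might infer that the protocol commits to a raw pooled correlation, but the text does not say so. What it does show is that the test is stated twice with its variables, that arm is named in neither place, and that arm is named for other analyses. Followed as written, the test mixes the two sources of correlation.

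The second reply is that hypothesis 2.2 claims only association. If both means shift, the marginal association really is positive, and rejecting zero is correct. This also stands. A reader might take 16% or 29% as the false-positive rate of the planned test, but they are error rates only if 2.2 is read as association among individuals given the same treatment. The case for that reading is that 2.2 sits under the objective on cortical mechanisms, where the between-arm part is already covered by 1.1 and 2.1.

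The third reply concerns the numbers. The article predicts no size for the TCI effect, and the SD of 5.2 is derived, not stated. Both are correct, so the figures are illustrations over a range. Nor is the correlation positive in every case: the formula gives an expected value, a sample r can be negative, and a negative within-arm relation could offset the shift.

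Finally, a reader might infer that change scores contaminate the correlation through their baselines. Nothing in the article shows this. Regression to the mean in each variable separately does not correlate the two changes unless their baselines or errors are related.

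**Conclusion.** The point holds as a weakness in a secondary-objective analysis. With no adjustment for arm, a correlation of TCI change with FMUE change over all participants has a positive expected value whenever BMP raises both outcomes and the changes are unrelated within arms. It therefore partly restates hypotheses 1.1 and 2.1 and says little about the mechanism. At the Table 2 detectable differences the artefact is modest, and about 84% of such trials would still be non-significant. It grows with the treatment effects and disappears if only one outcome moves. These sizes rest on zero within-arm correlation, 32 evaluable per arm, and the Table 2 SDs (or the pilot-based SD) taken as within-arm SDs of change. The primary FMUE analysis and the sample size are not affected.

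**What to change.** In Hypothesis 2a and 2b analysis, state that 2.2 is tested by the partial correlation of TCI change and FMUE change given treatment arm, or equivalently by a regression of FMUE change on TCI change with arm in the model. Baseline FMUE and baseline TCI may be added as covariates. Report the correlation and a scatterplot for each arm alongside. If a marginal correlation over all participants is also wanted, label it descriptive.

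The cost is a sentence or two of text and one degree of freedom for arm, or three with both baselines. No new data are needed, and the change fits the covariance framework already used for the other outcomes. The Discussion says analysis will follow once all participants have completed the trial, so the change can be recorded beforehand.

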### Interim analyses {21b}

Not applicable. At this time, we have no plans for an interim analysis.

### Methods for additional analyses (e.g., subgroup analyses) {20b}

As exploratory analyses, we will use linear regression models outcomes at 8 weeks post-treatment cessation as the dependent variable (FMUE, CAHAI-9, and TCI). These models will include treatment assignment (BMP vs. CP) and baseline outcome measure as a fixed-effects, as well as patient characteristics (age, low or high impairment severity at baseline, sex, and MEP status). We will examine differential impacts by fitting separate models with treatment-impairment severity, treatment-sex, and treatment-MEP status interactions. We will report relevant point estimates and standard errors for these models and conduct 5% level tests for interaction terms with two-sided alternative hypotheses.

### Methods in analysis to handle protocol non-adherence and any statistical methods to handle missing data {20c}

We will measure protocol adherence by the median number of repetitions of TST repetitions. Treatment therapists record the number of repetitions for each activity, and the data is de-identified and transferred to an excel sheet. Participants will be labeled as adherent if the median number of daily TST repetitions (over the 2-h visit) is equal to or greater than 100. Information about treatment activities is only available to non-blinded individuals.

Though we plan to follow up with patients repeatedly to minimize the amount of missing data, we expect some data may still wind up missing. Should greater than 5% of data be missing, we will explore missingness patterns via graphical analyses to evaluate potential mechanisms of missingness. If appropriate, multiple imputation will be used to handle missing data.

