### Outcomes {12}

Each participant is evaluated with primary and secondary outcome measures, TMS measures, and additional outcome measures at pre-intervention, post-intervention, and 8-week follow-up.

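### About 16% of 8-week outcomes are expected to be missing, yet the choice between complete-case ANCOVA and imputation waits on a look at the data, so the intent-to-treat label is not secured

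*Protocol article*

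**What the plan says.** All references are to the protocol article.

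- **Sample size {14}:** "We are enrolling 38 subjects per group", 76 in total, with 12 expected to be lost (given as 15%). It continues: "we project at least 32 subjects per group will have both the baseline and follow-up data required to compute our change outcomes". The 90% power is computed on 32 per group.
- **Statistical methods {20a}:** "We will use an intent-to-treat analysis for our primary and secondary analyses". The confirmatory model for FMUE and CAHAI-9 is a linear model with treatment and the baseline value of the outcome.
- **Missing data {20c}:** "Should greater than 5% of data be missing, we will explore missingness patterns via graphical analyses to evaluate potential mechanisms of missingness". Multiple imputation is then used if it is judged appropriate. The section does not say what would make it so.
- **Outcomes {12}:** primary, secondary, TMS and "additional outcome measures at pre-intervention, post-intervention, and 8-week follow-up". An intermediate FMUE score is therefore planned for every participant.
- **Discontinuation {11b}:** participants who withdraw from treatment are asked to attend the post-treatment and/or 8-week evaluations where this is not harmful.

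**The concern.** The 5% rule reads as a safeguard for an unlikely event, but the plan's own attrition figure makes that event the expected one. The rule then postpones the decision that matters: whether the primary result comes from those with an 8-week score or from everyone randomised. That decision would be made after outcome data have been inspected. The tool offered for it is graphs of the observed data, which cannot separate missing at random from missing not at random.

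Participants are not masked ({17a}) and may withdraw at any time ({11b}), so loss related to progress, and differing between arms, is possible. If it occurs, a completer comparison is biased. The post-intervention FMUE, a natural predictor of a missing 8-week value, plays no part in the stated model.

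**Working it through.** **1. The plan's own figure.** Inputs from Sample size {14} and Table 2: SD 8.11, R² = 0.2, 32 per group, two-sided 5%, 90% power.
- Residual SD = 8.11 × √(1 − 0.2) = 7.25.
- Standard error of the difference = 7.25 × √(2/32) = 1.81.
- Detectable difference from the noncentral t with 61 df = 5.97, against 5.98 stated. Power at 5.98 is 90.1%.
- Enrolment: 64 / (1 − 0.15) = 75.3, rounded up to 76.

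The sample-size arithmetic is sound, and the power rests on the 64 participants with both measurements.

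**2. Expected loss against the trigger.**
- Expected missing: 12/76 = 15.8%.
- Trigger: 5% of 76 = 3.8 participants, so four missing values cross it.
- Ratio: 12/3.8 = 3.2.

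**3. How selective loss becomes bias.** Suppose 6 of 38 are lost in one arm, and they would have scored d points worse on average than those who stayed. The completer mean in that arm is then too high by (6/38) × d = 0.158d:
- d = 2 gives 0.32 points
- d = 4.25 gives 0.67 points
- d = 6 gives 0.95 points

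The same loss in the other arm moves the estimated difference the opposite way.

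**4. Simulation.** Set-up: 38 per arm, 6 lost per arm with the post-intervention score observed, residual SD 7.25, true difference 6, 2,500 runs per scenario. The loss mechanism, its strength and the post/follow-up correlation are assumptions; the documents give none of them. Bias of completer ANCOVA in FMUE points:

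| Who is lost | r = 0.6 | r = 0.8 | r = 0.9 |
|---|---|---|---|
| Random, both arms | about 0 | about 0 | about 0 |
| Poor responders, equally in both arms | −0.02 | −0.06 | −0.01 |
| Poor responders, BMP arm only | +0.61 | +0.84 | +0.95 |
| Same, half the strength | +0.38 | +0.49 | +0.56 |
| Poor responders, control arm only | −0.67 | −0.91 | −0.95 |

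Monte Carlo error is about 1.81/√2500 = 0.04. These are not bounds: stronger assumed selection in the BMP arm gave 0.87 to 1.27.

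**5. Using the post-intervention score.** In the BMP-selective scenarios, a likelihood estimate that includes this score had bias of at most 0.07. This follows from the set-up, because loss was made to depend on that score. The standard error was 2-7% smaller under every mechanism. A direct check, with follow-up missing for 6 of 38 and the post score complete:
- Variance ratio = 1 − r² × (6/38).
- r = 0.6: √(1 − 0.36 × 0.158) = 0.97.
- r = 0.8: √(1 − 0.64 × 0.158) = 0.95.
- r = 0.9: √(1 − 0.81 × 0.158) = 0.93.

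This agrees with the simulation.

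**The case against.** The strongest reply is that nothing in the article restricts the analysis to completers. The 32 per group is a projection for power, which is ordinary practice, and not an analysis set. The article states intent-to-treat, provides for imputation, and seeks outcomes after withdrawal from treatment. This is correct. A reader might infer that the labelled intent-to-treat analysis simply is a completer analysis, and so contradicts itself. The documents do not support that. It becomes one only if imputation is judged inappropriate.

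A second reply is that the imputation model, its auxiliary variables, the covariance structure and the sensitivity analyses normally belong in an analysis plan, which is not shown. That also stands, and their absence is not counted here. What remains is the conditional rule that the article does state. An analysis plan that follows it inherits the discretion, and one that fixes a method departs from it.

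Third, baseline-adjusted ANCOVA is standard for a single follow-up contrast and, with multiple imputation, is valid under the same missing-at-random assumption as a repeated-measures model. This is accepted, and the fix allows either.

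Fourth, the direction of bias is unknown. A reader might conclude that completer ANCOVA would overstate the benefit by 0.6 to 0.9 points. That holds only if poor responders leave the BMP arm selectively, which no passage indicates.

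**Conclusion.** The concern holds in a limited form. Expected loss is about three times the plan's trigger. The method for handling it is left to a data-dependent judgement that graphs cannot settle, and the default is complete-case ANCOVA. The intent-to-treat label is therefore not secured; it is not shown to be false.

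At the planned loss, and under the assumed mechanisms, bias runs from about −1.0 to +1.0 FMUE points. That is up to one sixth of the 6.0-point hypothesis and a little over half of the 1.81-point standard error. It is near zero if loss is random or alike in both arms. The 2-7% gain in precision does not depend on the direction of loss, but it does require the post-intervention score to be observed in those lost later. The rule should be changed. The sample size is not in question.

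**What to change.** Replace the 5% threshold and the discretionary imputation step with one method, fixed before any unmasked analysis and applied to all randomised participants. Either of these would do:

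- a likelihood-based repeated-measures model with post-intervention and follow-up FMUE as outcomes; baseline FMUE, arm, visit and arm-by-visit as effects; unstructured covariance; and the primary contrast at 8 weeks; or
- the stated ANCOVA with unconditional multiple imputation that includes the post-intervention FMUE.

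Do the same for CAHAI-9 and TCI. Add a delta-based sensitivity analysis that shifts the missing values, separately by arm, to show how far the conclusion depends on missing at random.

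The cost is revised wording and modest programming, with no new data. The article says that analysis waits until all participants have completed, so on that schedule the change can be made in time. Two limits remain: the primary result still relies on missing at random, and participants lost before the post-intervention visit gain little from either method.
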